## Abstract

**Background::**

Movement and tone disorders in children and young adults with cerebral palsy are a great source of disability. Deep brain stimulation (DBS) of basal ganglia targets has a major role in the treatment of isolated dystonias, but its efficacy in dyskinetic cerebral palsy (DCP) is lower, due to structural basal ganglia and thalamic damage and lack of improvement of comorbid choreoathetosis and spasticity. The cerebellum is an attractive target for DBS in DCP since it is frequently spared from hypoxic ischemic damage, it has a significant role in dystonia network models, and small studies have shown promise of dentate stimulation in improving CP-related movement and tone disorders.

**Methods::**

Ten children and young adults with DCP and disabling movement disorders with or without spasticity will undergo bilateral DBS in the dorsal dentate nucleus, with the most distal contact ending in the superior cerebellar peduncle. We will implant Medtronic Percept, a bidirectional neurostimulator that can sense and store brain activity and deliver DBS therapy. The efficacy of cerebellar DBS in improving quality of life and motor outcomes will be tested by a series of N-of-1 clinical trials. Each N-of-1 trial will consist of three blocks, each consisting of one month of effective stimulation and one month of sham stimulation in a random order with weekly motor and quality of life scales as primary and secondary outcomes. In addition, we will characterize abnormal patterns of cerebellar oscillatory activity measured by local field potentials from the intracranial electrodes related to clinical assessments and wearable monitors. Pre- and 12-month postoperative volumetric structural and functional MRI and diffusion tensor imaging will be used to identify candidate imaging markers of baseline disease severity and response to DBS.

**Discussion::**

Our goal is to test a cerebellar neuromodulation therapy that produces meaningful changes in function and well-being for people with CP, obtain a mechanistic understanding of the underlying brain network disorder, and identify physiological and imaging-based predictors of outcomes useful in planning further studies.

**Trial registration::**

ClinicalTrials.gov
NCT06122675, first registered November 7, 2023.

## Background

Cerebral palsy (CP), an umbrella term for a group of disorders and posture caused by non-progressive brain disturbances (1), represents the most common physical disability of childhood, affecting one out of 323 children in the United States (1, 2). Movement disorders, including dystonia and choreoathetosis, occur in 15–17% of CP cases, a condition known as dyskinetic CP (DCP) (3). Mixed presentations are also common, as dystonia may be present to some degree in other CP forms, and DCP frequently has comorbid spasticity (4).

The treatment of movement disorders in DCP is challenging and frequently fails to meet patient needs. Oral medications generally have low efficacy in DCP and are limited by side effects (5, 6). Intrathecal baclofen improves dystonia, spasticity, and pain. However, it carries a high risk of infection and surgical complications compared to other surgical options, including deep brain stimulation (DBS) surgery (7). Selective dorsal rhizotomies, surgical interventions for predominantly lower limb spasticity, do not help dystonia and may even exacerbate it (8).

DBS surgery targeting the globus pallidus and motor thalamus has been increasingly used in individuals with acquired dystonia, including DCP, when other treatments are not effective or tolerated (9, 10). DBS is an invasive neuromodulation technique that targets pathological brain circuitries (11), and entails the implantation of bilateral electrodes into deep brain targets for the delivery of an electrical current via an impulse generator implanted in the chest. Pallidal and subthalamic DBS is Food and Drug Administration (FDA) approved under a Humanitarian Device Exemption in the United States for the treatment of chronic treatment-refractory primary dystonia. DBS offers advantages over other surgical therapies, including safety, reversibility, tolerability, and adaptability to the individual patient. DBS in traditional targets (globus pallidus and motor thalamus) can improve motor, disability and pain ratings in DCP, but motor and quality of life outcomes are highly variable and generally less beneficial than in isolated dystonia (5, 6, 9, 12–14). The relatively reduced benefit is thought to be partially related to implantation in targets with pre-existing structural damage and lack of effect on comorbid choreoathetosis and spasticity (6).

The cerebellum represents an attractive target for DBS in DCP since it has an increasingly recognized role in dystonia pathophysiology (15) and is frequently spared from hypoxic ischemic damage in DCP (16). Stimulation of cerebellar pathways improves dystonia in pre-clinical genetic animal models (17).

Cerebellar DBS for dystonia and spasticity in DCP arose from early reports of lesion-based surgeries and electrical stimulation published in the 1960s and 1970s (18–21). The reports showed an average 60–70% long-term improvement, although concerns existed regarding stimulator reliability and safety (22). More recent evidence using cylindrical DBS leads in the dentate nucleus have shown preliminary improvements in dystonia/choreoathetosis and even spasticity (18, 22–27). We recently reported surgical notes and preliminary outcomes in three subjects with DCP with bilateral cerebellar DBS, targeting the motor dentate nucleus and cerebellar outflow pathways (24). These individuals demonstrated improvements in objective movement rating scales, and subjective improvements in function without worsening in coordination. Other groups have reported successful and safe cerebellar DBS for other conditions, including cerebellar ataxia (28).

Here, we present the protocol for a single-center series of randomized, double-blinded N-of-1 trials studying cerebellar DBS for the treatment of severe movement and tone disorders in ten children and young adults with DCP. This trial is currently open for recruitment at the University of California, San Francisco (UCSF).

## Methods/Design

### Study Objectives

This study aims to ameliorate severe movement and tone disorders in CP by chronic neuromodulation (DBS) of motor dentate nuclei and cerebellar output pathways. The efficacy of cerebellar stimulation for improving quality of life (QOL) and motor outcomes will be tested by periodic clinical assessments and objective kinematic metrics. In addition, we will characterize abnormal patterns of cerebellar oscillatory activity as measured by local field potentials (LFP), and evaluate candidate imaging markers of baseline disease severity and response to DBS by performing pre- and 12-month postoperative volumetric structural and functional MRIs.

#### Study Design and Setting

This is a single-center series of randomized, double-blinded N-of-1 trials to test the effects of chronic DBS of dentate and cerebellar output pathways on severe movement and tone disorders in DCP. This study will recruit ten children and young adults aged 7–25 with DCP secondary to hypoxic ischemic static encephalopathy (HIE). We will implant Medtronic Percept^™^, an FDA-approved “bidirectional” neurostimulator that can sense and store brain activity while delivering DBS therapy.

We will use a series of N-of-1 clinical trials to enhance causal inference and mitigate the variability in clinical features in this population (Fig. 1). We will use a cross-over design and compare three months of effective stimulation with three months of sham stimulation for each patient. We will administer the trea^™^ents in blocks of two months with one month per condition (sham vs. effective stimulation) in a randomized order. During these one-month trials for each condition, patients, caregivers, and assessing clinicians will be blinded to the state of the stimulator, and outcomes will be measured at weekly intervals. To evaluate kinematic metrics, we will use videotaped automated movement recognition techniques and formal gait analysis.

This protocol was developed to adhere to the Standard Protocol Items: Recommendations for Interventional Trials (SPIRIT) extension for N-of-1 trials (SPENT) checklist that is aligned with the CONSORT (consolidated reporting items for trials) extension for N-of-1 trials (CENT, 29).

### Recruitment and Participant Selection

Participants will be recruited from the UCSF Movement Disorders and Neuromodulation Center and the Pediatric Neurology Clinics at UCSF Benioff Children’s Hospitals in San Francisco and Oakland, California, USA. Our UCSF Movement Disorders and Neuromodulation Center includes a multidisciplinary clinic with a special focus on surgical therapies and has a long history of successful recruitment for surgical trials in movement disorders.

The inclusion criteria include a diagnosis of DCP with or without comorbid spasticity (Gross Motor Function Classification System, GMFCS, Levels II-V), with a clear history of hypoxic ischemic brain injury preceding motor symptoms made by a pediatric neurologist, with supporting MRI findings, sparing the cerebellum. Potential participants will have a history of appropriate therapy with oral medications with inadequate relief, and severe enough movement disorders to warrant consideration for DBS therapy.

Exclusion criteria include medical conditions significantly increasing surgical risks, uncontrolled epilepsy, pregnancy, severe fixed contractions and skeletal deformities, and CP etiologies apart from HIE (for example, genetic mimics of cerebral palsy, absence of documented risk factors for HIE, traumatic brain injury or history of infectious or autoimmune encephalitis).

### Informed Consent

All participants are required to give informed consent prior to enrollment. Assent will be sought from all involved minor participants and adults who are not capable of consent. The context of the specific neurological condition and neurosurgical treatment proposed in this research project may make it difficult for patients and families to distinguish between procedures that are essential to their clinical care and similar procedures that are undertaken solely for research purposes. In this study, participants may have impaired cognition and need careful assessment of capacity for research participation as well as for treatment. For this purpose, this study will use a “teach-to-goal” consent framework (30–32). Teach-to-goal is an educational strategy in which the informed consent document is reviewed with prospective participants, who then answer questions about critical elements of the study. Misperceptions are corrected and the participant’s comprehension is assessed again. Consent from a surrogate from those individuals who cannot demonstrate comprehension after several attempts is then sought. Adult patients, especially those without known intellectual disability, will be presumed to have capacity to consent. However, if an adult patient is known to have intellectual disability or if during the consent process, questions arise regarding the ability to consent, the capacity to consent to participate in the study will be formally determined.

#### Retention Plan

Our retention strategies include: maximizing convenience for patients by integrating research visits with routine clinical care wherever possible, having all study clinicians, researchers, and coordinators in a single location, ensuring cost-neutrality for the participant and family, and maintaining motivation by providing frequent updates to participants and their families on the progress of the study.

### Study Outcomes

For this clinical trial, there is a primary QOL and a primary motor outcome. The QOL endpoint will be the within- and between-child difference in Caregiver Priorities & Child Health Index of Life with Disabilities (CPCHILD) QOL scale total standardized score (33), while on intervention (effective stimulation) versus placebo (sham stimulation). The rationale for this QOL primary outcome measure is that health-related QOL measures provide a more complete picture of an individual than motor assessments alone. Health-related QOL measures have been shown to help medical decision-making and have been used in practice to evaluate patients’ responses to interventions and allow providers to focus on the areas that are most important for the child and family (13). The primary motor outcome will be the within- and between-child difference in the global index score of the Movement Disorder Childhood Rating Scale 4–18 Revised (MD-CRS 4–18-R, (34)). This is a scale specifically designed for the assessment of movement disorders for children and young adults with secondary dyskinetic movement disorders such as DCP (34).

Key secondary outcome measures will be individual CPCHILD domain scores, other health-related QOL scores (Burke-Fahn-Marsden Dystonia Rating Disability subscale, PedsQL^™^ scores, and Clinician and Patient Global Impression of Change scales), other motor and spasticity ratings (Burke-Fahn-Marsden Dystonia Rating Motor subscale, Unified Dystonia Rating Scale, Dyskinesia Impairment Scale, Hypertonia Assessment Tool, and Modified Ashworth Scale scores), and exploratory automatic video kinematic and gait analyses. See Table 1 for a summary of assessments.

#### Sample Size

The power calculation (35) is based on the more variable CPCHILD score. Standardized CPCHILD scores, which range from 0 (best) to 100 (worst), will be calculated for each of the scale’s seven domains and the total survey (calculated by dividing raw scores by the maximum item score, multiplied by 100). We chose a 10-point difference as a clinically relevant difference between sham and effective stimulation (13). Assuming normally distributed differences and treatment-by-patient interaction standard deviation of 12.6 based on previously published data (36), relatively stable disease and minimal carry-over of effects, and a type I error rate of 0.05 (two-sided), a chosen sample size of n=10 would have over 80% power to detect clinically relevant differences.

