### Statistical Analysis

The primary analysis will use the N-of-1 trials to obtain individual and population-level estimates of the efficacy of cerebellar DBS in ameliorating movement disorder symptoms and in improving QOL for children and young adults with DCP. We will use an intention-to-treat analysis. We anticipate that, within each participant, within-arm CPCHILD and MD-CRS 4–18-R scores measuring the effects of cerebellar stimulation will be relatively stable over time, with slopes approximately parallel with some possible carryover from the effective to sham stimulation arm, based on our prior experience with cerebellar DBS(24). Based on weekly assessments, each participant will contribute 4 values per arm per block. Within each block, we will treat the participant’s arm-specific values as simultaneous replicates and attribute them to the midpoint of the relevant follow-up interval.

To accommodate alternatives to Gaussian distributions of the measured outcomes, we will analyze them using a generalized linear mixed model (GLMM), with treatment arm, and follow-up time as fixed effects and the subject as a random effect. With 3 blocks per arm, an arm-by-time interaction is unlikely to be needed but will be evaluated in a sensitivity analysis; we will also consider a simplification of the model that substitutes blocks for time. Output of the model will include estimates of the participant-specific mean (95% confidence interval) difference between arms, as well as the overall mean difference (95% confidence interval) between arms and overall plot. An interim analysis of the success of cerebellar stimulation will be performed after the first set of 2 subjects is studied.

The N-of-1 trial design is particularly useful when treatment effects exhibit variability between individuals (38), as is the case for DBS for complex movement disorders in DCP(10). N-of-1 designs provide the most rigorous evidence for treatment decisions at the individual level. In addition, when outcomes are aggregated from several patients, N-of-1 trials can yield treatment effect estimates applicable to the broader population, and close to the level of evidence of randomized controlled trials (39). While not previously used in DBS for dystonia, the N-of-1 design was found to be useful for assessing DBS efficacy in neuropathic pain (40), and it has been more recently recommended for uncommon movement disorders (41).

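### The claimed power of over 80% does not follow from the stated inputs: 10 patients and an interaction SD of 12.6 give at most about 61% for a 10-point CPCHILD difference

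*Protocol article*

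**What the plan says.** All the inputs stand in the Sample Size section of the protocol article.

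- **Effect:** "We chose a 10-point difference as a clinically relevant difference between sham and effective stimulation".
- **Variability:** "Assuming normally distributed differences and treatment-by-patient interaction standard deviation of 12.6 based on previously published data". No within-patient SD is given.
- **Other assumptions:** "relatively stable disease and minimal carry-over of effects", with a two-sided type I error of 0.05.
- **Result:** "a chosen sample size of n=10 would have over 80% power to detect clinically relevant differences".

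The design is described in the Abstract (Methods): "Each N-of-1 trial will consist of three blocks, each consisting of one month of effective stimulation and one month of sham stimulation". The Statistical Analysis section adds four weekly ratings in each arm of each block. It plans a generalized linear mixed model that names subject as the random effect, and it promises both individual and population-level estimates. The same section says that, once results from several patients are aggregated, "N-of-1 trials can yield treatment effect estimates applicable to the broader population".

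**The concern.** The SD is named as a treatment-by-patient interaction. That is the spread of true treatment effects across patients, and it sets a floor under the standard error of the average effect that depends only on the number of patients. Ten patients with a spread of 12.6 points looked too few to detect a 10-point mean difference with 80% power.

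This is the only power statement in the article, and it is said to rest on the more variable of the two primary outcomes. If it is too high, the population-level comparison is presented as adequately powered when it has a substantial chance of missing the difference that the plan itself calls clinically relevant. A non-significant result could then be taken as evidence against the treatment when the trial was simply too small to tell.

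**Working it through.** **Inputs (Sample Size section):** difference d = 10; interaction SD ψ = 12.6; n = 10; two-sided α = 0.05. From the Abstract, k = 3 blocks. The within-patient SD σ is not given. It is set to 0 first, which is the most favourable case and amounts to unlimited replication within each patient.

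**Formula.** Each patient yields one mean effective-minus-sham difference. The variance of the average over patients is

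Var = (ψ² + 2σ²/(k·m)) / n,

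where m is the number of independent ratings per arm per block. Blocks and weekly ratings divide only the σ² term; ψ² is divided by n alone.

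**Attempt to reproduce the stated figure (σ = 0).**

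- Standard error = 12.6/√10 = 3.98.
- Non-centrality = 10/3.98 = 2.51.

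| Test | Power |
|---|---|
| Two-sided t, 9 df | 60.9% |
| Two-sided normal approximation | 70.9% |
| One-sided t, 9 df | 74.9% |
| One-sided normal approximation | 80.6% |

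Only the one-sided normal approximation passes 80%, and the plan specifies a two-sided test.

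**Adding within-patient error.** The σ values below are assumptions, since the article gives none. Power is by two-sided t on 9 df.

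| Assumed σ | One independent value per period (m = 1) | Four independent weekly values (m = 4) |
|---|---|---|
| 5 | 56.7% | 59.8% |
| 8 | 51.2% | 58.2% |
| 10 | 46.9% | 56.7% |
| 12.6 | 41.2% | 54.5% |

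Example for σ = 10, m = 1: the SD of a patient's mean difference is √(12.6² + 2·100/3) = 15.01.

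**What 80% power would take (σ = 0).**

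| Quantity | t test | Normal approximation |
|---|---|---|
| Patients, at d = 10 and ψ = 12.6 | 15 | 13 |
| Detectable difference, at n = 10 and ψ = 12.6 | 12.5 | 11.2 |
| Largest SD, at n = 10 and d = 10 | 10.0 | 11.3 |

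By the t test, 14 patients give 78.4% and 15 give 81.5%.

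**Other readings of 12.6.**

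- *Within-patient period SD, no interaction.* The SD of a patient's mean difference is 12.6·√(2/3) = 10.29, and the standard error is 10.29/√10 = 3.25. Power is 78.1% (t, 9 df), 83.2% (t, 20 df), 85.6% (t, 58 df) or 86.7% (normal).
- *SD of a single block's difference, averaged over three blocks, no interaction.* The SD is 12.6/√3 = 7.27, and power is 97.1% (t, 9 df).

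These readings can exceed 80%, but neither is an interaction SD, and both set the variation in effect between patients to zero.

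**The case against.** The strongest reply is that the label may be wrong and the power right. Read as a within-patient SD over three blocks, 12.6 gives 78% to 87% depending on the degrees of freedom, and most of those variants reproduce the claim. The method and the SD are both cited to sources not shown, so the article alone cannot settle which is in error. That stands, and the fix must allow for it. It does not clear the sentence, though: the SD would be misnamed, and the calculation would assume that all patients respond alike. The Statistical Analysis section justifies the N-of-1 design on the ground that effects differ between individuals.

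A second reply is that 61% depends on a paired t test, whereas the plan specifies a mixed model and fixes no degrees of freedom; a large-sample test would give 71%. That is fair as a description of the range. The 71% figure treats the SD as known, however. With the variance estimated from 10 patients, using the normal cut-off would push the type I error above the stated 5%. Neither figure reaches 80%.

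A third reply is that the model names only subject as a random effect, so the interaction would not enter the standard error, and for the average effect in these ten patients it need not. That holds for these ten patients and for the individual estimates. It does not hold for the population-level estimate the plan also promises: with a true spread of 12.6 points, omitting it understates the standard error and inflates the type I error.

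Finally, the article reports estimates with confidence intervals and does not say that a null result will be read as no effect. That is correct; misreading is a risk, not something the plan states.

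**Conclusion.** The concern holds. With 12.6 as labelled and the stated two-sided 5% level, no calculation reaches 80% power at n = 10. The best case is 61% by the t test, about 19 points short, or 71% by the normal approximation, about 9 points short. Both assume no within-patient error.

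By the t test, the chance of missing a true 10-point mean difference is therefore at least 39%, against the under 20% implied. Anything above 39% depends on a within-patient SD that the article does not give. Under an assumed SD of 10, the chance is 43% if the four weekly ratings are independent and 53% if that SD applies to the period as a whole.

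The conclusion rests on the population mean effect being the target and on 12.6 being what the article calls it. If it is something else, the error lies in the label and in the missing between-patient component, and the sentence still needs correcting.

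**What to change.** First establish what 12.6 measures in its source, then make one of two changes in the Sample Size section.

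1. **If it is the interaction SD,** replace the power claim with: *With n = 10 and a treatment-by-patient interaction SD of 12.6, power for a 10-point mean difference is at most about 60% (two-sided 0.05, t test); the difference detectable with 80% power is about 12.5 points.*
2. **If it is a within-patient or single-block SD,** rename it, add an assumed interaction SD with its basis, and recompute power with both components, for example from (ψ² + 2σ²/(k·m))/n.

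In either case state the formula, the within-patient SD used, and how the three blocks and weekly ratings enter.

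The cost is wording, plus a short recalculation under the second option. Enrolment, design and treatment do not change. Under the first option the stated power becomes less favourable; under the second it depends on the interaction SD assumed.
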